# Study protocol: NeoCLEAR: Neonatal Champagne Lumbar punctures Every time – An RCT: a multicentre, randomised controlled 2 × 2 factorial trial to investigate techniques to increase lumbar puncture success

**DOI:** 10.1186/s12887-020-02050-8

**Published:** 2020-04-15

**Keywords:** Neonate, Lumbar puncture, Meningitis, Preterm infant, Technique, Stylet

## Abstract

**Background:**

The neonatal period carries the highest risk of bacterial meningitis (~ 1 in 5000 births), bearing high mortality (~ 10%) and morbidity (20–50%) rates. Lumbar puncture (LP) remains essential to the diagnosis of meningitis. Though LP is a common procedure in neonates, success rates are lower (50–60%) than in other patient populations. None of the currently-practised neonatal LP techniques are supported by evidence from adequately-powered, randomised controlled trials (RCTs). NeoCLEAR aims to compare two modifications to the traditional technique which are free, accessible, and commonly practised: sitting (as opposed to lying) position, and ‘early’ (as opposed to ‘late’) stylet removal.

**Methods/design:**

Written parental informed consent permitting, infants in neonatal/maternity wards, of 27^+ 0^ to 44^+ 0^ weeks corrected gestational age and weighing ≥1000 g, who require an LP, will be randomly allocated to sitting or lying position, and to early or late stylet removal. The co-primary objectives are to compare success rates (the proportion of infants with cerebrospinal fluid red cell count < 10,000/mm^3^ on first LP procedure) in 1020 infants between the two positions, and between the two methods of stylet removal. Secondary outcomes relate to LP procedures, complications, diagnoses of meningitis, duration of antibiotics and hospital stay. A modified intention-to-treat analysis will be conducted.

**Discussion:**

Two modifications to the traditional LP technique (sitting vs lying position; and early vs late stylet removal) will be simultaneously investigated in an efficient and appropriately-powered 2 × 2 factorial RCT design. Analysis will identify the optimal techniques (in terms of obtaining easily-interpretable cerebrospinal fluid), as well as the impact on infants, parents and healthcare systems whilst providing robust safety data. Using a pragmatic RCT design, all practitioners will be trained in all LP techniques, but there will inevitably be variation between unit practice guidelines and other aspects of individual care.

An improved LP technique would result in:

• Fewer uninterpretable samples, repeated attempts and procedures

• Reduced distress for infants and families

• Decreased antibiotic use and risk of antibiotic resistance

• Reduced healthcare costs due to fewer procedures, reduced length of stay, shorter antibiotic courses, and minimised antibiotic-associated complications

**Trial registration:**

ISRCTN14040914. Date assigned: 26/06/2018.

## Background

Neonatal bacterial meningitis has high rates of mortality and morbidity in Europe and North America, and higher still in Africa and Asia [1]. The symptoms and signs are non-specific in neonates, and the diagnosis can only be confirmed by analysing cerebrospinal fluid (CSF), following lumbar puncture (LP). Infants with meningitis typically require 14–21 days of inpatient intravenous antibiotics, incurring significant financial costs, and often receive hospital follow-up due to the risk of long-term neurological sequelae [2]. Prolonged antibiotic use is associated with significant complications [3, 4]. If meningitis can be excluded, antibiotics are usually stopped after 5 days, allowing discharge with no further follow-up.

Each year up to 30,000 UK newborn infants undergo LP [5], but success rates are much lower in neonates (50–60%) [6, 7] than older children (78–87%) [8, 9]. Interpretation of non-clear CSF samples containing significant numbers of red blood cells (RBC) (> 5000, or > 10,000 RBC/mm^3^) is challenging and the presence/absence of meningitis difficult to confirm. Thus, LPs often need repeating, and lead to treatment with extended courses of antibiotics because meningitis cannot be excluded.

LP techniques currently vary by local practice. Several modifications to ‘traditional’ technique have been investigated, but few have good evidence of benefit. Two modifications identified during a literature review appeared the most promising and amenable to investigation in an RCT:
Sitting position, in which the infant is held in a semi-upright, sitting position compared to lying (‘lateral decubitus’) position.‘Early stylet removal’ (ESR), which is the removal of the stylet from the LP needle shaft once it has penetrated the subcutaneous tissue, and before advancing the needle into the CSF.

Sitting: the only published systematic review regarding LP in children/neonates examined sitting position and concluded that “Positions other than the lateral decubitus may be equal or superior in terms of lumbar puncture success” …and… “A large-scale prospective clinical trial directly addressing LP success and safety in different positions would clarify the need to change current practice” [10].

Stylet removal: traditional technique aims to insert the needle into the CSF space, before removing the stylet (‘late stylet removal’ (LSR)). If the needle has advanced too far, unintentional puncture of the anterior venous plexus can cause a blood-stained tap. ESR has therefore been adopted by some practitioners but is only backed by observational evidence [8, 9].

Other literature suggests no consistent evidence of significant benefit for: training in LP [11, 12]; seniority of practitioner [8, 9, 13–16]; sedation [13, 17]; local anaesthetic [8, 9, 12, 15, 18, 19]; and formulae for needle insertion depth (except certain subgroup analyses) [20]. Although there is growing evidence for ultrasound assistance [21–25], the equipment and training required has hindered widespread adoption. In comparison, sitting position and ESR are straightforward and already used by some practitioners.

### Aims

We aim to determine the optimal technique for lumbar puncture in newborn infants by evaluating the success rate, short-term clinical, resource, and safety outcomes of two modifications to traditional LP technique: infant position (sitting vs lying) and timing of stylet removal (early vs late).

This would be the first appropriately-powered RCT investigating neonatal LP technique and would therefore make a significant contribution to current knowledge.

## Methods/design

### Aim & Design

This is a pragmatic, multicentre, 2 × 2 factorial RCT to compare the proportion of infants with CSF obtained and RBC count < 10,000/mm^3^ on the first LP procedure when sitting position is adopted compared to lying position, and when ESR is performed compared to LSR. Other clinical decisions will be made according to local protocols. Clinicians undertaking LPs will receive training in the different trial techniques. Once a decision is made to perform an LP as part of routine care, parents of eligible infants will be approached to discuss consent. If given, randomisation will proceed. Staff will be advised to undertake 1–2 attempts (defined as the needle passing through the skin once) per ‘procedure’. The randomised technique will be used for up to two procedures. The requirement and timing for a second or any further procedures will be determined by the clinical team. Data will be collected from hospital records, and recorded on trial specific electronic case report forms (eCRFs). All samples sent to the laboratory will follow local site procedures, with relevant data from the laboratory reports inputted onto eCRFs. The trial rationale and design were closely discussed with and received input from local parent representatives from the local Support for the Sick Newborn And their Parents (SSNAP) charity [26].

The trial includes an internal pilot, which was based in centres recruiting the first 250 randomised infant participants in the first 8 months, in order to optimise study processes around recruitment, intervention delivery, training, and outcome assessments. The Trial Steering Committee (TSC) reviewed pilot data and have made recommendations and approved continuation.

The trial design is summarised in Fig. 1.

**Fig. 1 Fig1:**
[figure not shown]
Study flowchart

### Setting & participants

Infants who are having an LP in UK neonatal units and their maternity wards.

### Inclusion criteria

Parent(s) willing and able to give informed consentInfants of corrected gestational age (CGA) from 27^+ 0^ weeks to 44^+ 0^ weeks, AND working weight of 1000 g or moreFirst LP for current indication

### Exclusion criteria

Unable to be held in sitting position (including infants intubated and mechanically-ventilated) or other clinical condition which is likely, in the opinion of the treating clinician, to make sitting difficult, or which is likely to be compromised by sitting (e.g. open gastroschisis).Previously randomised to the trial

### Schedule of study procedures

**Table Taba:** 

Tasks	Visits			
	Screening	First LP	Further LPs (if needed)	Discharge
Eligibility confirmed	X			
Informed consent	X			
Randomisation	X			
STAI-S (Parent Questionnaire)^a^	X	X		
Data collection to eCRF	X	X	X	X
Serious/Adverse Event assessments		X	X	

^a^Internal pilot sites to complete following consent (before first LP) and within 48 h after first LP

### Primary outcome

The proportion of infants with successful first LPs (RBC count fewer than 10,000/mm^3^ in CSF on first procedure).

### Secondary outcomes

The following short-term clinical, resource and safety outcomes have been defined as:
The proportion of infants with:
No CSF obtained, or pure blood/clotted, or blood-stained, or clearCSF obtained and RBC count < 500, < 5000, < 10,000, or < 25,000 /mm^3^, or any RBC countA CSF white blood cell (WBC) count not requiring a correction (whatever the RBC count)Total number of procedures and attempts performed per infantProportion of infants diagnosed (by WBC count criteria, culture, Gram stain, and/or clinically) via CSF with:
Meningitis: WBC count 20 or more in CSF, or a true positive culture/Polymerase Chain Reaction (PCR) (if RBC count is ≥500, the WBC count will be reduced by 1 for every 500 RBC counts to give a ‘corrected’ WBC count)Equivocal: WBC count (or corrected WBC) < 20, AND negative (or contaminated/incidental) culture and PCR with:
Either Polymorphonuclear leukocytes (PMN) > 2 (and RBC count < 500)OROrganism found on Gram stainNegative: WBC (or corrected WBC) count < 20, PMN ≤2 (if RBC count < 500), and negative (or contaminated/incidental) cultures, PCR, and Gram stainUninterpretable: No CSF obtained, or clotted, or CSF so bloody or insufficient that a cell count was impossibleCSF WBC, RBC, corrected WBC counts, PMNs and lymphocytes from the clearest sampleTime taken on first procedure from start of cleaning skin to removing needle at end of all attemptsInfant movement on first procedure using a basic 4-point scale

### Outcomes related to cost and safety

In all infants, according to CSF-defined and clinically-defined diagnostic criteria:
Duration of the antibiotic courseLength of stay in surviving infantsImmediate complications related to LP:
Cardiovascular instability, including oxygen saturations and heart rateRespiratory deterioration (escalating respiratory support) post-LPFor the pilot phase: parental anxiety (State Trait Anxiety Inventory - State Subscale (STAI-S) Questionnaire)

### Screening and recruitment

Infants who are having an LP will be screened for eligibility. Anonymised screening data will be recorded via the randomisation website for the Coordinating Centre to review rates of ineligibility and participant uptake rates.

Parents of eligible infants will be provided with both verbal and written information in a Parent Information Leaflet by their clinical team. Parents with legal parental responsibility will be approached to discuss the trial, answer any questions they may have and to request consent. Parents will have as much time as they need to consider and discuss the information with the research team, or other independent parties to decide whether to participate in NeoCLEAR. Written informed consent for the study will be obtained by a suitably qualified member of the study team. Parents completing the STAI-S will also be asked to provide written consent for their participation. Consent will be given at such time to allow randomisation and enable the clinical team to prepare for that procedure. Where this is not possible, the LP will not be delayed if the infant’s clinician deems any delay to be clinically unsound: in such cases, the infant would not be recruited to NeoCLEAR.

### Randomisation and blinding

Infants will be randomised 1:1:1:1 to one of the four arms: (1) Lying (lateral decubitus) position and LSR; (2) Lying position and ESR; (3) Sitting position and LSR, or (4) Sitting position and ESR, using a 24/7 secure web-based randomisation facility which will ensure balance between the groups. A telephone backup system will be available 24 h a day.

Stratified block randomisation will be used to ensure balance between the groups with respect to the collaborating hospital and CGA at trial entry (four groups: 27^+ 0^–31^+ 6^/32^+ 0^–36^+ 6^/37^+ 0^–40^+ 6^/41+ weeks). Where repeat (second) LPs are warranted, they will receive the same allocated technique. Multiple births will be randomised separately with their study ID numbers linked on the database prior to analysis.

A statistician independent of the trial will generate the randomisation schedule and the Senior Trials Programmer will write the web-based randomisation program; both will be independently validated. The implementation of the randomisation procedure will be monitored by the Senior Trials Programmer throughout the trial and reports will be provided to the Data Monitoring Committee (DMC).

This is an open-label trial as blinding of the practitioner and nursing staff to the allocated technique is not possible. The assessment of the primary outcome and major secondary outcomes will be based on laboratory tests (effectively blinded). Parents will not usually be told which technique their infant has been allocated, and are not routinely present for the procedure; however if they request this, it will be shared with them and they may observe the LP at the discretion of the practitioner.

### Baseline assessments

Trial entry data will include details to confirm eligibility and confirmation of parental written consent. During the pilot phase, after consent but before the first LP, the parent was asked to complete a 5-point Likert scale ‘How have you felt physically during the last couple of days?’, and STAI-S questionnaire [27, 28]. STAI-S is a well-validated measure consisting of 20 questions that identify how stressed/anxious someone is feeling at the time of assessment. All items are rated on a 4-point scale, the mean score will be used in analyses. Discontinuation of the STAI-S was recommended by the TSC based on a review of the pilot.

### Subsequent data collection

Most outcome data for this trial are routinely recorded clinical items obtained from the clinical notes. Non-routinely collected data includes procedural details such as time taken, infant movement, oxygen saturation and heart rate. No additional blood or tissue samples are required for this trial. All data will be collected using trial specific eCRFs. Outcome data will be collected until discharge home. Parents completing the STAI-S will be asked to complete a second questionnaire within 48 h following the first LP.

### Sample handling

As per best practice, all samples from any attempt should be sent to the microbiology laboratory for standard lab analyses, even if bloody or only 1–3 drops obtained, as culture may be informative.

### Description of procedure

Participating infants will require LP as part of routine care; NeoCLEAR randomisation will specify the technique used. Training will attempt to standardise other potential confounders, including needle type and analgesia. Practitioners will be trained and given written best practice guidance on technique, including recommendations for LP variables. However, adherence will not be mandatory, and will be captured in the trial eCRFs.

The first LP should be performed within the same shift as randomisation where possible, to minimise bias, in 1–2 attempts. If a second LP is required, the same technique should be employed. The need for any further procedures will be determined by the consultant.

### Safety reporting

An independent DMC will be established to review the study data and outcomes including safety reports of Serious Adverse Events (SAEs). The DMC will ensure the safety and wellbeing of the trial participants and make recommendations to the TSC regarding continuance of the study or modification of the protocol. The TSC will have ultimate responsibility for deciding whether the trial should be stopped on safety grounds. SAEs will be collected until the infant is discharged home, as SAEs occurring after this time point should not relate to the trial intervention. As parental participation is limited to the STAI-S questionnaire, no SAE recording will be conducted for this group.

The following are known, but rare, complications of LP: any occurrence following the LP should be reported as an SAE:
Iatrogenic meningitisIatrogenic haemorrhage: spinal haematoma (symptomatic), intraventricular, intracerebral and subarachnoid haemorrhageCerebral herniationNerve damage

The full protocol and Guidance Sheets provided to sites also pre-specify expected SAEs that are foreseeable in the trial population, and will not be reported unless thought to be causally related to trial procedures.

All unforeseeable SAEs occurring after consent until discharge home must be reported.

### Discontinuation and withdrawal

Parents have the right to withdraw consent for any aspect of the study, including their infant’s future procedures and data collection, or their own questionnaire completion. The treating clinician may discontinue a participant if they consider it to be in the best interests of the infant’s health and wellbeing.

### Definition of end of study

The end of the trial will be defined as the date when the trial database is locked. An end of trial declaration will be made to REC.

### Project management

The study is sponsored by the University of Oxford. The trial will be run by the NPEU CTU, based at the University of Oxford and the CI. On a day-to-day basis, the trial will be run by a Project Management Group (PMG) according to NPEU CTU SOPs and will be subject to audit and inspection. The core PMG will meet every month, either remotely or face-to-face. An extended PMG (Co-Investigator Group) will meet regularly to troubleshoot, review progress and forward plan. The PMG reports to the TSC.

The trial will be overseen by the TSC which will have ultimate responsibility for considering and, as appropriate, acting on the recommendations of the DMC. The TSC will include an independent chair, at least one clinician, statistician and Patient and Public Involvement (PPI) representative, and the CI. The TSC will meet at least annually and review the progress of the trial.

The DMC will be independent of the study and the TSC. The DMC will review the progress of the trial and interim analysis at least annually, and make recommendations on the conduct of the trial to the TSC.

### Patient and public involvement

Patient and public representatives have been extensively involved in trial planning, grant/protocol writing, and preparing study materials. Advice from two PPI co-applicants from local charity SSNAP [26] included aspects of protocol design, wording in parent-facing documentation, as well as ongoing recruitment initiatives. Contributions on documentation were also received from Bliss baby charity [29]. A lay person is a member of the TSC, and will be involved in trial oversight and dissemination of findings.

### Statistics and analysis

#### Sample size and power calculation

Four hundred eighty-three infants are required for each arm of the main comparison (sitting vs lying position and ESR vs LSR), to detect a 10% absolute difference (from 59 to 69%) in the proportion of infants with successful LPs, with 90% power, a 5% two-sided significance level and assuming (based on expert opinion and the lack of external evidence) no interaction effect between infant position and timing of stylet removal. Allowing for 5% attrition, the required recruitment target is 1020 (255 in each of the four groups). The 59% control event rate was derived from local prospective cohort data [30] and corroborated by published UK data [20]. We estimate 50% parental uptake rate and minimal ‘loss to follow-up’ as all data will be collected pre-discharge.

Modelling suggests we will need 10 local Neonatal Units and Neonatal Intensive Care Units to recruit enough infants within 24 months, with a recruitment rate of around 5 infants per centre per month assuming: staggered starts (two centres per month), and each centre taking 4 months to reach stable recruitment rate. PMG will implement recruitment initiatives and additional centres, based on actual recruitment.

Our inclusion/exclusion criteria are designed to minimise protocol deviations by only including infants who can be sat up. Only sparse safety data is available for LPs < 27 weeks and < 1000 g; hence these infants will be excluded from our trial.

#### Description of statistical methods

Outcomes for participants will be analysed in the groups to which they are assigned regardless of deviation from the protocol or allocation received, but will be excluded from the analysis if no LP procedure was received (modified intention-to-treat analysis). To assess the effect of position we will compare groups (1–Lying/LSR) plus (2–Lying/ESR) with groups (3–Sitting/LSR) plus (4–Sitting/ESR), and to assess the effect of the timing of stylet removal we will compare groups (1) plus (3) with groups (2) plus (4). We will calculate the risk ratio (95% Confidence Interval (CI)) for the primary outcome (and all other dichotomous outcomes), the mean difference (95% CI) for normally distributed continuous outcomes or the median difference (95% CI) for skewed continuous outcomes. Absolute risk difference and CIs will also be calculated for tested dichotomous clinical outcomes (to be presented in a supplementary appendix). Groups will be compared using regression analysis, adjusting for the stratification variables used at randomisation. Both crude and adjusted estimates will be presented but the primary inference will be based on the adjusted analyses. Adjusted risk ratios will be estimated using log-binomial regression, or a Poisson regression model with a robust variance estimator in the event of non-convergence. Linear regression will be used for normally distributed outcomes and quantile regression for skewed continuous outcomes.

With a view to minimising the effects of multiple testing given the number of procedures and attempts performed for each infant, and correlation between some outcomes, statistical inference will be restricted to a predefined list of tested outcomes. Summary data by trial arm will be provided for all other outcomes but statistical tests (or the calculation of CIs) will not be performed. A complete list of outcomes that will be tested and not tested statistically are provided in a supplementary appendix.

Full details of the statistical analysis will be documented in the Statistical Analysis Plan.

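### The general model gives the pre-LP STAI-S score no stated role; if post-LP parental anxiety is formally compared, the pre-LP score should be a covariate (a minor gain in precision)

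*Protocol article*

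**What the plan says.** **Model.** Under Description of statistical methods the article sets one adjustment rule without distinguishing between outcomes: "Groups will be compared using regression analysis, adjusting for the stratification variables used at randomisation". Crude and adjusted estimates are both to be shown, with primary inference resting on the adjusted ones. Linear regression is named for normally distributed outcomes and quantile regression for skewed ones. Randomisation and blinding identifies the stratification variables, the aim being "balance between the groups with respect to the collaborating hospital and CGA at trial entry". Neither measures parental anxiety, and no outcome-specific covariate is named anywhere.

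**Questionnaire.** The footnote to the schedule of procedures reads "Internal pilot sites to complete following consent (before first LP) and within 48 h after first LP". Baseline assessments confirms the first time point ("after consent but before the first LP, the parent was asked to complete") and Subsequent data collection the second ("Parents completing the STAI-S will be asked to complete a second questionnaire within 48 h following the first LP"). Parental anxiety is listed, for the pilot phase, under Outcomes related to cost and safety. On scoring, the article says "All items are rated on a 4-point scale, the mean score will be used in analyses", without saying what part the pre-LP score plays.

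**Limits on scope.** The same methods section confines inference to a list of outcomes fixed in advance and held in an appendix that is not shown. Other outcomes get summaries by arm, without tests or confidence intervals. Full analysis detail is left to the SAP. Baseline assessments adds: "Discontinuation of the STAI-S was recommended by the TSC based on a review of the pilot".

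**The concern.** The trial obtained a pre-procedure measurement of a continuous outcome from the same parent, on the same instrument. Applied as written, the general rule compares post-LP scores after adjusting for hospital and CGA group alone. State anxiety may vary between parents for reasons unrelated to LP technique, and the pre-LP score can absorb some of that variation where the stratification variables cannot.

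At stake is the width of the confidence interval for the effect of position and of stylet timing on parental anxiety, if such an interval is calculated. Leaving the score out also lets any chance difference between groups in pre-LP anxiety carry, in part, into the estimate from this one sample. With the questionnaire confined to the pilot, more data would not make good the lost precision; the choice of model can.

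**Working it through.** **Figures in the plan.** The article gives no STAI-S standard deviation (SD), pre–post correlation, target difference or number of completers, so there is no STAI-S figure to reproduce. The primary sample size does reproduce. For 59% against 69%, two-sided 5% and 90% power, with pooled variance:

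n = [1.960 × √(2 × 0.64 × 0.36) + 1.282 × √(0.59 × 0.41 + 0.69 × 0.31)]² / 0.10² = 483 per side after rounding up.

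Then 966 / 0.95 = 1017 after rounding up, against the stated 1020 (4 × 255). None of this depends on STAI-S.

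**Inputs for the check.**
- Number of parents, N: the article says "The trial includes an internal pilot, which was based in centres recruiting the first 250 randomised infant participants in the first 8 months". Taking one parent per infant, 250 is an approximate ceiling. N = 100 is an assumed lower case.
- Allocation is 1:1:1:1, so each factorial comparison is 1:1.
- Correlation ρ between pre-LP and post-LP scores, given the stratification variables: assumed 0.3, 0.5 and 0.7.
- Differences are in units of the post-LP SD.

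**Formulae (linear regression, large-sample).**
- Variance factor from adding the pre-LP score: 1 − ρ².
- Standard error: SE = √(1 − ρ²) × √(4/N).
- Difference detectable with 80% power at two-sided 5%: (1.960 + 0.842) × SE.
- Equivalent number of parents without the covariate: N / (1 − ρ²).

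**Results at N = 250.**

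| ρ | Variance factor | SE (SD units) | Detectable difference | Equivalent N | Power for an assumed 0.3 SD |
|---|---|---|---|---|---|
| score not used | 1.00 | 0.126 | 0.354 | 250 | 66% |
| 0.3 | 0.91 | 0.121 | 0.338 | 275 | 70% |
| 0.5 | 0.75 | 0.110 | 0.307 | 333 | 78% |
| 0.7 | 0.51 | 0.090 | 0.253 | 490 | 91% |

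Example for ρ = 0.5: √0.75 × √(4/250) = 0.866 × 0.1265 = 0.110, and 2.802 × 0.1095 = 0.307.

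**Results at N = 100.** The detectable difference is 0.560 SD without the pre-LP score, and 0.535, 0.485 and 0.400 SD with it at ρ = 0.3, 0.5 and 0.7.

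The reduction in variance is therefore 9%, 25% or 49% whatever N is. If STAI-S is only summarised by arm, no estimate is made and no precision is lost.

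**The case against.** The strongest reply is that the article states a general rule in condensed form and leaves full detail to a SAP that is not shown. A baseline covariate for one secondary questionnaire is ordinary SAP content. Several stronger readings are tempting, and the documents do not support them:

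- *That the pre-LP score is excluded or will go unused.* The article names no other covariate, but it does not say that others are ruled out. The sentence on using the mean score follows directly on the pre-LP questionnaire and is not confined to the post-LP one.
- *That anxiety will certainly be tested.* The list of tested outcomes is not shown. A pilot-only outcome whose discontinuation was recommended may well be on the untested list.
- *That every pilot parent supplied a score.* Screening and recruitment requires the parent's own consent for the questionnaire, and the Discussion says completion was not pursued if a parent became distressed. The number of completers is unknown.
- *That the comparison would be biased.* Randomisation keeps the estimate without the pre-LP score unbiased in expectation; only precision suffers.
- *That post-LP scores would be tabulated alone.* No section says so, so there is nothing to correct in the summaries.

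It is also fair to say that the percentages come from assumed correlations and would apply to any pre–post measure.

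All of this makes the point smaller and conditional but does not remove it. The article is not silent on adjustment: it fixes a covariate set and rests primary inference on it, and that set as written lacks a baseline that the trial collected.

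**Conclusion.** The point holds in conditional form and is minor. If post-LP STAI-S is among the formally compared outcomes, the model as stated gives a valid estimate that is less precise than the data allow. The variance saving forgone is 9% to 49% for assumed correlations of 0.3 to 0.7. At the approximate ceiling of 250 parents, the detectable difference would fall from 0.354 SD to between 0.338 and 0.253 SD.

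These figures rest on the assumed correlations, on linear regression (they do not carry over directly if the score is treated as skewed and analysed by quantile regression), and on both questionnaires being available for the parents counted. If STAI-S is on the untested list, the point falls away. In either case the primary outcome, the 483 per side and the 1020 target are unaffected.

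**What to change.** Add one sentence to the statistical methods, or confirm it in the SAP: where post-LP STAI-S is formally compared between groups, the pre-LP STAI-S mean score is included as a covariate in addition to hospital and CGA group, and the adjusted difference is reported with its 95% CI. If STAI-S is on the untested list, no change is needed.

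The cost is one covariate in one secondary model. It needs no new data, since the pre-LP questionnaire was already part of the pilot, and no change to the sample size or the primary analysis.
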